## Abstract

**Background:**

Helminths are a major global health issue, impacting health, educational, and socioeconomic outcomes. Infections, often starting in childhood, are linked to anemia, malnutrition, cognitive deficit, and in chronic cases of *Opisthorchis viverrini* (OV), cholangiocarcinoma. The main control strategy for helminth infection is mass drug administration; however, this does not prevent reinfection. As such, prevention strategies are needed. The “Magic Glasses” is a school-based cartoon health education package that has demonstrated success in improving knowledge, attitudes, and practices (KAP) surrounding soil-transmitted helminths (STH) in China and the Philippines. This study is designed to assess the acceptability and impact of the 2 new versions of the Magic Glasses targeting STH and OV designed for the Lower Mekong audience in Cambodia, Lao People’s Democratic Republic (PDR), and Thailand.

**Objective:**

The objective of this study is to evaluate the acceptability of the “Magic Glasses Lower Mekong” and “Magic Glasses Opisthorchiasis” education packages among schoolchildren in the Lower Mekong Basin, and the impact of these education packages on students’ KAP surrounding STH and OV, respectively.

**Methods:**

Schoolchildren will be recruited into a cluster randomized controlled trial with intervention and control arms in rural schools in Cambodia, Lao PDR, and Thailand. Schoolchildren’s initial acceptability of the intervention will be evaluated using an adapted questionnaire. Sustained acceptability will be assessed at 9-month follow-up through focus group discussions with students and interviews with teachers. Impact will be evaluated by KAP questionnaires on STH and OV. KAP questionnaires will be administered to children at baseline and at follow-up. Indirect impact on parents' KAP of OV and STH will be assessed through focus group discussions at follow-up.

**Results:**

The trial is in progress in Lao PDR and Thailand and is expected to commence in Cambodia in January 2024. The results of the study are expected to be available 18 months from the start of recruitment. We hypothesize that participants enrolled in the intervention arm of the study will have higher KAP scores for STH and OV, compared with the participants in the control arm at follow-up. We expect that students will have initial and sustained acceptability of these intervention packages.

**Conclusions:**

This trial will examine the acceptability of the “Magic Glasses Opisthorchiasis” and “Magic Glasses Lower Mekong” interventions and provide evidence on the effectiveness of the “Magic Glasses” on KAP related to OV and STH among schoolchildren in the Lower Mekong Basin. Study results will provide insight on acceptability and impact indicators and inform a scaling up protocol for the “Magic Glasses” education packages in Cambodia, Lao PDR, and Thailand.

**Trial Registration:**

Australian New Zealand Clinical Trials Registry ACTRN12623000271606; https://www.anzctr.org.au/Trial/Registration/TrialReview.aspx?id=385315&isReview=true

**International Registered Report Identifier (IRRID):**

DERR1-10.2196/55290

## Introduction

### Background

Helminthiases, or infections caused by parasitic worms, are a major global health concern [1]. Communities impacted by poverty and located in tropical regions, such as the Lower Mekong Basin (LMB; a region including Cambodia, Lao People’s Democratic Republic [Lao PDR], and northeast Thailand) are particularly vulnerable to such infections. The most common helminthiases in the LMB are soil-transmitted helminths (STH)—including *Ascaris lumbricoides*, *Trichuris trichiura*, and hookworm (*Ancylostoma* spp. and *Necator americanus)*—and *Opisthorchis viverrini* (OV), commonly known as the Southeast Asian liver fluke [2]. Reported prevalence of STH infections have reached 74% (227/308) [3], 83% (134/162) [4], and 28% (24/85) [5], in Cambodia, Lao PDR, and Thailand, respectively. OV is estimated to affect 10 million people in the LMB, the highest reported burden globally [6,7]. Several studies have reported high incidence of helminthiases among preschool- and school-aged children (SAC), often with high infection intensity [2,8-11]. Kaewpitoon et al [2] reported overall STH prevalence of 11.88% (233/1957) among SAC in the LMB in 2015; however, in some areas, prevalence reached 16.08% (152/945). Given the low sensitivity of the Kato-Katz thick smear technique used (particularly for low intensity infections), it is also possible that infection prevalence in the region was underestimated [12]. While there is limited research on OV burden in children, Yoshida et al [13] reported an OV infection rate of 39% (64/164) among children in secondary school in Vientiane, Lao PDR. Helminthiases are associated with stunting, malnutrition, anemia, chronic pain, fatigue, and cognitive deficit [14-17]. In addition, chronic OV infections are causally linked to cholangiocarcinoma, a cancer of the bile duct [18]. Transmission route varies by helminth type: STH is typically transmitted via contact with egg-infected soil, such as consumption of contaminated fruit or vegetables, or playing in contaminated outdoor spaces [19]. OV is transmitted via ingestion of raw or undercooked infected freshwater cyprinid fish [20]. The primary control strategy for STH and OV infection is mass drug administration (MDA); STH infection is typically treated with benzimidazole anthelmintics [19]. Treatment efficacy varies against species: cure rates exceed 90% for *Ascaris*, 50% for hookworm species [21], and 25% for *Trichuris* [22]. The recommended treatment for OV is praziquantel [23]. Several studies have found praziquantel to be highly efficacious against OV infection, with cure rates exceeding 90% [24,25]. However, while MDA is effective in treating helminthiases, it does not prevent reinfection. As such, further measures such as education on helminth control and prevention are needed.

Children are an important group for targeted behavioral and educational interventions. Between the ages of 5 and 12 years, children undergo major cognitive growth, including the formation of beliefs and attitudes [26,27]. Health education during this period can inform long-term habits and behaviors [26-28]. SAC are also a well-placed group for intervention delivery, as schools are institutions trusted by children and their families, and can facilitate delivery to a large population, as recognized in World Health Organization’s (WHO) Global School Health Initiative [29].

The “Magic Glasses” is a school-based cartoon health education package that has demonstrated success in improving STH knowledge and attitudes, improving water, sanitation, and hygiene (WASH) practices and reducing disease burden in affected communities [30,31]. The intervention is designed to be relatable and engaging for children, with the cartoon set in the local context, and the protagonists being schoolchildren who learn about STH transmission, symptoms, treatment, and prevention as they explore their community [30,31]. The original “Magic Glasses” in China achieved major improvements in self-reported STH knowledge, attitudes and behaviors, as measured by a knowledge, attitudes, and practices (KAP) questionnaire: the intervention group scored 24.9 percentage points higher than the control after adjusting for baseline scoring (95% CI 23.4-26.4; *P<*.001) [31]. Overall KAP scores were inversely correlated with STH infection, with uninfected students scoring 9.9 percentage points higher than infected students (95% CI 5.8-14.0; *P<*.001) [31]. With respect to infection burden, the intervention led to a 50% decrease in STH incidence among intervention schools (odds ratio 0.5, 95% CI 0.35-0.70; *P<*.001) [31]. From 2016 to 2017, the “Magic Glasses” educational package was adapted for the Philippines, a country with estimated 33% STH prevalence [30]. “Magic Glasses Philippines” led to significant improvements in knowledge and behavior among intervention schools scoring 5.5 percentage points higher than control schools in the knowledge component of the KAP questionnaire (56.8, 95% CI 55.7-57.9 vs 51.5, 95% CI 50.3-53.7; *P<*.001) and 1.1 percentage points higher in the behavioral component (87.2, 95% CI 86.6-87.9 vs 86.1, 95% CI 85.4-86.8; *P*=.002) [30]. With respect to disease burden, the intervention achieved a 60% reduction in the odds of any STH infection in intervention schools with a baseline prevalence <15% (adjusted odds ratio 0.4, 95% CI 0.20-0.70; *P<*.001), although it is important to note that the intervention did not significantly reduce odds of infection when higher prevalence schools were included [30]. Following the success of the “Magic Glasses Philippines” trial, the intervention is now being recommended for roll-out across the Philippines as part of the school curriculum.

The present study is designed to assess the acceptability of 2 new “Magic Glasses” cartoons, developed for the LMB, and their impact on schoolchildren’s self-reported KAP of STH and OV. Several studies have identified acceptability as a key indicator for initial and sustained intervention success [32-36]. However, there remains a lack of consistency among acceptability measures and definitions in public health research. Sekhon et al [37] developed the Theoretical Framework of Acceptability (TFA), and defined acceptability as “a multi-faceted construct that reflects the extent to which people delivering or receiving a healthcare intervention consider it to be appropriate, based on anticipated or experienced cognitive and emotional responses to the intervention” [37]. The TFA outlined 7 domains of acceptability, “affective attitude, burden, perceived effectiveness, ethicality, intervention coherence, opportunity costs, and self-efficacy” [37]. In order to conduct a robust assessment of all the domains of acceptability, the acceptability of the intervention will be assessed using mixed methods. Quantitatively using an adapted version of the TFA questionnaire [38] and qualitatively using focus group discussions (FGDs) with schoolchildren and key informant interviews (KIIs) with teachers. The KAP questionnaire will be administered at baseline and follow-up to assess the impact of the intervention, and the intervention coherence domain of acceptability.

### Aims

While previous Magic Glasses studies have demonstrated the impact of the cartoon in improving KAP surrounding helminths, a more detailed assessment of acceptability is required. Firstly, this study aims to determine whether the “Magic Glasses” OV and STH video education packages will be acceptable to schoolchildren and their teachers in LMB. Secondly, this study will be the first “Magic Glasses” to target OV, in addition to STH. Finally, this study aims to determine the impact of the “Magic Glasses” cartoons on students’ KAP on OV and STH infection.

## Methods

### Trial Design

The trial is a cluster randomized controlled trial (cRCT) with 2 arms, intervention and control. As the intervention will be delivered through schools, a cRCT design was chosen for practical reasons and to minimize contamination. Each school participating in the trial is a “cluster.” Schools will be randomly allocated to intervention and control. Schools in the intervention arm will receive the “Magic Glasses” education package developed for LMB, consisting of “Magic Glasses Opisthorchiasis” (MGO) and “Magic Glasses Lower Mekong” (MGLM), in addition to the standard health education activities in accordance with local government guidelines. Schools in the control arm of the study will receive the standard health education activities only in accordance with local government guidelines.

### Ethical Considerations

The study will be conducted in accordance with the ethical principles of the Australian National Statement on Ethical Conduct in Human Research [39]. Prior to data collection, an information sheet detailing the purpose of the study, potential risks, research contact information, and informed consent form in the local language will be distributed to parents and caregivers. Only schoolchildren who have provided informed assent and parental consent will be included in the study. Participants will not receive compensation for their involvement in the study but will be able to withdraw at any time. In the case that a participant does withdraw from the study, their responses will not be used in analyses. All quantitative data will be collected on paper questionnaires. Qualitative data (KIIs, FGDs) will be recorded using audiotapes and transcribed. To protect participant privacy, all responses will be deidentified prior to data analyses.

The study protocol was submitted to and received ethical approval from the Australian National University Human Ethics Committee (approval number 2022/507), the Cambodia Ministry of Health National Ethics Committee for Health Research (N197NECHR dated June 27, 2023), the Lao PDR Ministry of Health National Ethics Committee for Health Research, and Khon Kaen University Ethics Committee for Human Research (HE651147, record number 4.2.03:16/2565). The study is registered at Australian New Zealand Clinical Trials Registry (ANZCTR): ACTRN12623000271606.

### Setting

The trial will be conducted in rural primary schools in Preah Vihear Province, Cambodia; Savannakhet Province, Lao PDR, and Khon Kaen Province, Thailand. To maximize homogeneity within each country, schools will be recruited from the same district where possible. To minimize the risk of contamination, all control and intervention schools will be at least 3 km apart.

### Participants

A total of 684 schoolchildren in Grades 3-6 from randomly selected schools in Cambodia, Lao PDR, and Thailand will be recruited into the study cohort and followed up approximately 9 months after baseline. During the follow-up period, 1 teacher and 3-5 parents will be recruited from each intervention school.

### Eligibility Criteria

Among the recruited schools, children across Grades 3-6 who provided consent and assent will be eligible for this study.

### Consent and Recruitment

Based on local expertise on school student numbers in each country, approximately 6 schools will be selected in each country to achieve a total sample size of 228 per country. Prospective schools will be selected in consultation with the local departments of education. Once schools are identified, permission to conduct the study will be sought from the principal of each selected school. Teachers and parents or legal guardians of prospective participants will then receive an information sheet outlining the procedure and purpose of the study and contact information, and a consent form. On receiving the written parental or guardian consent, the aims, process, and outcome of study will be explained to prospective student participants and their written assent will be sought. Only schoolchildren who have provided informed assent and parental consent will be included in the study. Teachers and parents will be recruited a month before follow-up. As part of the recruitment process, an information sheet will be provided and informed consent will be sought. Once written consent is obtained, teachers and parents will be recruited into the study.

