#### Follow-Up

All participants in control and intervention schools will be recruited for follow-up approximately 9 months after baseline. Participants will complete the same questionnaires for OV and STH to assess the impact of the interventions on KAP for the respective diseases. KAP scores will also provide insight on acceptability domains of intervention coherence and perceived effectiveness. In intervention schools, impact and acceptability will also be assessed using qualitative measures. FGDs will be conducted with a subset of schoolchildren in the original cohort to discuss the sustained acceptability and effectiveness of each cartoon. FGDs will also be conducted with parents of participants to investigate the indirect impact of the MGO and MGLM intervention packages on parents' knowledge of OV and STH, respectively. KIIs will be held with teachers to discuss the acceptability and impact of the cartoons on health-related attitudes and behavior.

Follow-up assessments will employ the same delivery timing as used at baseline and intervention delivery to ensure consistency and minimize confusion between OV and STH.

The trial study design is shown in Figure 2. See Multimedia Appendices for anticipated delivery times for each country.

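### Adult recruitment shortly before the follow-up questionnaires, in intervention schools only, may prompt one arm ahead of the primary KAP outcome

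*Protocol article*

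**What the plan says.** Three places in the protocol article bear on this.

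- **Consent and Recruitment** fixes the time: "Teachers and parents will be recruited a month before follow-up". It describes the contact as follows: "As part of the recruitment process, an information sheet will be provided and informed consent will be sought". The same section has an earlier contact before baseline, not limited to one arm: "Teachers and parents or legal guardians of prospective participants will then receive an information sheet outlining the procedure and purpose of the study".
- **Participants** fixes the arm and the number: "During the follow-up period, 1 teacher and 3-5 parents will be recruited from each intervention school".
- **Follow-Up** sets the pupil measurement for both arms: "All participants in control and intervention schools will be recruited for follow-up approximately 9 months after baseline". It then adds work in one arm: "In intervention schools, impact and acceptability will also be assessed using qualitative measures". That work is focus groups with pupils, focus groups with parents and interviews with teachers. The pupils come from the cohort that supplies the primary outcome: "FGDs will be conducted with a subset of schoolchildren in the original cohort to discuss the sustained acceptability and effectiveness of each cartoon". On order, the section says: "Follow-up assessments will employ the same delivery timing as used at baseline and intervention delivery".

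Data Analysis names the OV and STH KAP scores as the primary outcome. Blinding says blinding is not possible, and the Discussion extends this to research staff and notes that the data are self-reported.

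**The concern.** Taken together, the Participants and Consent and Recruitment sections place a study contact in one arm, about eight months after baseline and about a month before the primary outcome. Teachers are approached for interviews about the acceptability and impact of the cartoons, and parents for discussions that cover their knowledge of OV and STH. A consent process will ordinarily disclose that purpose in some form.

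The teacher has seen the cartoons with the class and the pupils were given pamphlets, so the means to revisit the topic are at hand. A parent may raise it at home.

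The follow-up comparison is meant to show what pupils keep some months after the reinforcement session, which takes place 6-8 weeks after first delivery. A late reminder confined to intervention schools is not part of the defined package. Because it coincides exactly with arm, the analysis could not separate it from the package's own effect. The expected direction favours the intervention. The limitations in the Discussion cover social desirability and lack of blinding, but not this contact.

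**Working it through.** **Reading the passages together**

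- *Arm.* The timing sentence in Consent and Recruitment does not name an arm. Participants does, and it names only intervention schools.
- *Time.* Consent and Recruitment puts the approach before follow-up. Participants puts it within the follow-up period. The two agree if that period means the interval running up to the nine-month assessment. They disagree if it means the assessment itself.
- *Balance.* The pre-baseline information sheet goes to teachers and parents of prospective participants generally. It does not offset a later contact made in one arm.
- *Order at follow-up.* At baseline the two questionnaires are on separate days, and in intervention schools each package follows its own questionnaire on the same day. If follow-up copies this, a discussion of the first topic could fall before the second topic's questionnaire. Nothing requires that order, and nothing excludes it.

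**Illustration of size**

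The plan gives no figure for this contact, and its sample size does not enter the argument. Inputs from the document:

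- about 6 schools and 228 pupils per country (Consent and Recruitment)
- 3-5 parents and 1 teacher per intervention school (Participants)
- Grades 3-6 (Participants) or years 3-5 (Power)
- target difference of 5 percentage points in knowledge (Power)

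Assumptions: equal school and grade sizes, one cohort child per recruited parent, every intervention school affected alike, and the cue sizes themselves.

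Shift in arm mean = share of pupils reached × assumed cue.

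*Pupils per school:* 228 / 6 = 38.

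*Parents:* 3/38 = 7.9% and 5/38 = 13.2% of pupils.

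| Assumed cue (points) | Shift with 3 parents | Shift with 5 parents |
|---|---|---|
| 2 | 0.16 | 0.26 |
| 5 | 0.39 | 0.66 |
| 10 | 0.79 | 1.32 |

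Against 5 points this is 0.16/5 = 3% to 1.32/5 = 26%.

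*Teacher of one grade, recap worth 1-3 points to that grade:*

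- four grades: 1/4 × 1 to 1/4 × 3 = 0.25 to 0.75 points
- three grades: 1/3 × 1 to 1/3 × 3 = 0.33 to 1.0 points

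Against 5 points this is 0.25/5 = 5% to 1.0/5 = 20%. The two routes can reach the same pupils, so they are not added. The 5-point yardstick is for knowledge, whereas the primary score also counts attitude and behaviour.

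**The case against.** The strongest reply is that cueing is supposed, not shown. The recruitment contact is an information sheet and a consent request to a few adults. It is not made to pupils, and the sheet's content is not given. That stands: the document supports a one-sided risk, not an established bias.

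The assumed cues can also be called generous. The Introduction reports the whole Philippines package as worth 5.5 points in knowledge and 1.1 in behaviour. A consent sheet to a parent would hardly add 10, so the lower rows of the parent range are the more plausible ones. This stands too.

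A reader might infer that focus groups will come before a KAP questionnaire. The document does not say so. Follow-Up describes the questionnaires first, and the baseline pattern completes each topic's questionnaire before anything else on that topic. A discussion of liver fluke has no obvious route to a higher STH score, because transmission differs and the scores are analysed separately. The trial-profile figure and the appendix of dates are not available here and may settle the order. This part is therefore secondary.

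A reader might also credit a teacher's recap of 1-3 points to every pupil, which would be 20-60% of the target. The plan recruits one teacher per school for a cohort spread over three or four grades and does not say whom that teacher teaches, so the larger figure has no support.

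The reply does not remove the recruitment rule itself. It is stated outright, applies in one arm and precedes the primary outcome.

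**Conclusion.** The point holds as an avoidable, one-sided risk of bias created by a stated rule. That the contact falls in intervention schools only and before the follow-up KAP measurement is well supported, subject to the looser timing phrase in Participants. That pupils in one arm are in fact cued, or that the between-arm difference is in fact inflated, is not supported and should not be claimed.

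The size cannot be derived from the document. Under the stated assumptions the illustrative shift is about 0.2-1.3 points through parents and about 0.25-1.0 points through a teacher of one grade, set against a 5-point target. These figures show that the risk need not be trivial; they do not estimate it.

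It would also go too far to say that advance notice spoils the parent focus groups. They are qualitative, are held in one arm without a comparator, and need some notice whenever consent is sought.

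**What to change.** - **Consent and Recruitment:** state that teachers and parents are approached, informed and asked for consent only after pupils in that school have completed both the OV and the STH follow-up questionnaires. If that cannot be arranged, make an identical, neutrally worded contact in control schools at the same time. This is second best, because control schools have no package to revisit.
- **Participants:** align the timing phrase with the revised rule.
- **Follow-Up:** state that all pupil and parent focus groups and all teacher interviews take place after the second KAP questionnaire in that school.

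Apply this wherever follow-up has not yet been held. Cambodia had not started when the article was written, while Lao PDR and Thailand were under way, so the procedure could differ by country. Schools are allocated within country, so such a difference would not be confounded with arm, but it should be recorded.

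The change reorders steps already planned and alters no sample size. The cost is a short amendment, somewhat later qualitative sessions and possibly a second visit to intervention schools.
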